#### Trial intervention

When all of the procedures at the inclusion visit are performed, the patients are sent to the investigator responsible for assessing vascular function (PWV, AI, and CBP), randomization, and delivery of the study medication (12-week supply). Vascular function parameters are measured by the same trained investigator to ensure consistency and homogeneity.

Before administration of the drug, the investigator explains the most common adverse events (headache and orthostatic hypotension) to the patient.

After randomization, a single 40-mg dose of extended-release isosorbide mononitrate is administered between 9:30 and 10:30 am during the first 6 weeks. Study patients attend three visits after randomization. The first is at 6 weeks from baseline, when clinical parameters are assessed. These include BP (seated and standing), resting pulse, and the Morisky-Green test. All adverse events are recorded, regardless of their relationship to the study medication. If the objective (SBP <140 mmHg) is not reached, the dose is titrated to 60 mg/d (single dose); otherwise, the 40-mg dose is maintained.

After 12 weeks of treatment, the study is considered to have finished, except in the case of patients who withdraw prematurely. At the final visit, the parameters recorded are PP, SBP, DBP, heart rate and ambulatory BP. Compliance is also evaluated using the Morisky-Green test, and the investigator questions the patient about adverse events, orthostatic hypotension, and other treatments taken during the study. Vascular function parameters (CBP, AI, and PWV) are measured between 2 and 5 days before the final visit while the patient is still taking the medication.

Figure 1 shows the study flow-chart.

**Figure 1 F1:**
[figure not shown]
Study flow-chart.

#### Evaluation of effectiveness

The study drug is considered effective if PP decreases significantly with respect to placebo according to the primary objective.

Secondary efficacy is assessed based on the improvement in vascular function parameters, the percentage of patients achieving control of BP at the clinic and with ABPM, and the change in PP measured by ABPM. All objectives are measured based on the comparison of values from the baseline and final visits.

#### Ethics

The planning and conduct of this trial are subject to national legislation. The trial is performed in accordance with the Guidelines of the World Medical Association (WMA), the Declaration of Helsinki (1996), the Guidelines of GCP (CPMP/ICH/135/95), and the stipulations of national drug and data protection laws and other applicable regulatory requirements.

The investigator is responsible for ensuring that no patient undergoes any study-related examination or activity before either the patient or the legal guardian has signed an informed consent document. Detailed information is provided to the patient/legal guardian before consent is given.

The investigator must inform the patient of the aims, methods, anticipated benefits, and potential hazards of the study, including any discomfort it may entail. The investigator must inform patients that in providing informed consent, they are giving permission for representatives of the trial site coordinating investigator or regulatory authorities to inspect their medical records to verify the information collected. The patient must be given every opportunity to clarify any points he/she does not understand. Patients or legal guardians must sign and date the informed consent form. Patients who refuse to give or withdraw their written informed consent are either not included or do not continue to participate in the study.

In accordance with Spanish legislation (RD 223/2004 of 6 February), a civil liability insurance policy has been taken out to cover possible adverse events arising from the study medication that could affect the trial subjects.

#### Evaluation of safety

The most common adverse events are headache, orthostatic hypotension, somnolence, dizziness, and asthenia. These generally disappear with continued treatment. Less common or rare adverse events include bradycardia, angina pectoris, acute hypotension and syncope, nausea, vomiting, exfoliative dermatitis, allergic reactions, and flushing. Overdose can produce hypotension, tachycardia, cyanosis, shock, seizures, vomiting, agitation, respiratory failure, bradycardia, and methemoglobinemia.

The period for reporting an adverse event starts when the study drug is administered and ends with the last follow-up visit. The association between an adverse event and the trial medication must be classed as related or not related to the study drug by a study physician.

Adverse events considered related to the study medication are monitored until resolution or until the event is considered stable. All related adverse events that result in a participant’s withdrawal from the study or are present at the end of the study should be monitored until resolution. It is left to the investigator’s clinical judgment whether or not an adverse event is of sufficient severity to warrant the participant’s withdrawal from treatment.

This study is performed without an external sponsor under the coordination of the scientific committee and under the supervision of a safety committee, which is blind to the intervention. The safety committee is composed of three physicians, each of whom is an expert in hypertension. The committee also includes a biostatistician and expert in bioethics.

#### Sample size calculation

Sample size is predetermined based on the effect the variable PP, which is the primary objective. According to the results of the Starmans-Kool trial [17], the PP after treatment could be 87 mmHg in the placebo group and 79 mmHg in the experimental group, both with a standard deviation of 16 mmHg. In order to obtain a power of 80% to detect differences using a *t* test for independent samples, with an α risk of 5%, the sample size for each group must be 64 patients. Considering losses of 20% of recruited individuals, which could weaken the sample for some secondary objectives, we decided to increase the sample size by this percentage, although all the tests are performed by intent to treat. For this reason, the final sample size for each group is 77 patients.

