#### Randomization, blinding, and assignment to treatment groups

Subject numbers are assigned sequentially as each patient enters the study. Subjects are assigned to the study drug through a randomization schedule based on the randomization plan. The study drug is stored under the conditions specified on the label in a locked, safe area of the pharmacy department to prevent unauthorized access.

Both the study drug and the placebo are indistinguishable; they are manufactured by the same company and are similar in appearance, organoleptic characteristics, and presentation.

In the event of an emergency, the investigator decides whether it is necessary to unblind the subject’s treatment assignment using the unblinding envelopes provided to the hospital and/or pharmacy. If unblinding is necessary, the investigator or study pharmacist must record the reason for unblinding, as well as the date and time of the event.

During the study, the events considered sufficient reason for unblinding are as follows: admission to hospital or visit to the emergency department related to the study drug. The patients can be removed from the study without unblinding in the following circumstances: withdrawal of consent, major adverse event(s), ineligibility (arising either during the study or retrospectively after having been overlooked at screening), significant protocol deviation, disease progression requiring discontinuation of the study medication or inability to continue to comply with study procedures, loss to follow-up, or death. Each participant has the right to withdraw from the study at any time, for any reason, and with no repercussions for his/her medical care.

In the case of unblinding, the analyses are based on an intent-to-treat population, which includes all randomized subjects. Because the percentage of lost participants was predicted in the calculation of sample size, lost patients need not be replaced during follow-up. The person analyzing the results remains blind to the patient’s group.

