## Discussion

ISH remains difficult to control in many cases, despite the availability of various types of appropriate medication; however, most are able to reduce SBP, albeit with a considerable associated reduction in DBP. The consequent severe side effects, such as reduced coronary perfusion and orthostatic hypotension, limit treatment options.

Hypertension continues to be the most important cardiovascular risk factor today, and cardiovascular illnesses are the main cause of death in developed countries, especially among people over 65.

The results of our trial should demonstrate whether treatment with isosorbide mononitrate improves not only control of arterial pressure, but also vascular function in patients with refractory ISH. If our hypotheses are proved, a clinical trial with morbidity and mortality as the main end-points would be justified. Such a trial could also be used to investigate the long-term effects of this drug.

Few clinical trials have been carried out to test oral nitrates in patients with ISH, even though these agents seem to be effective and have been used over long periods in the treatment of other illnesses, such as ischemic heart disease, hypertensive emergency, or acute lung edema.

Our trial is performed on a collaborative basis between the hospital (center for recruitment and vascular function tests) and the primary care center, because most of these patients have their main contact with the health service through their primary care physicians. A collaboration of this type makes it easier to reach patients and provides more robust results with greater external validity.

Our study is subject to three limitations. First, potentially high loss to follow-up because of non-fatal side effects; however, this is compensated for, as it was taken into account in the sample size calculation. Second, in the long term, patients could develop tolerance to nitrates, although this was not demonstrated in any of the trials we reviewed. Finally, our trial was not designed to demonstrate reductions in morbidity and mortality; rather, our main objective was to evaluate tolerance and effects on some intermediate variables.

In conclusion, treatment of ISH with extended-release isosorbide mononitrate could improve control of SBP with minimal side effects, thus helping to reduce the morbidity and mortality of the disease.

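### The 20% loss allowance multiplies 64 by 1.2 instead of dividing by 0.8, so at the assumed loss 77 per group leaves 61 to 62 patients with outcomes, slightly below the 64 the plan derives (minor)

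*Protocol article*

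**What the plan says.** All the inputs are in the protocol article under Sample size calculation. Pulse pressure after treatment "could be 87 mmHg in the placebo group and 79 mmHg in the experimental group", "both with a standard deviation of 16 mmHg". The test is an independent-samples t test. The power target is introduced by "In order to obtain a power of 80% to detect differences" and the significance level by "with an α risk of 5" percent, with no statement of sidedness. The result is 64 per group.

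The section then assumes that 20% of recruited patients will be lost, remarks that this could weaken the sample for some secondary objectives, and continues: "we decided to increase the sample size by this percentage, although all the tests are performed by intent to treat". It concludes: "For this reason, the final sample size for each group is 77 patients".

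Two other places refer back to this allowance:

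- Randomization, blinding, and assignment to treatment groups: "Because the percentage of lost participants was predicted in the calculation of sample size, lost patients need not be replaced during follow-up".
- Discussion, first limitation, on possibly high loss to follow-up: "however, this is compensated for, as it was taken into account in the sample size calculation".

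**The concern.** A loss stated as a fraction of patients recruited is offset by dividing the required number by the fraction retained. Adding the same percentage to the required number always falls short, because the loss then acts on the larger, inflated total. The article states the base of the percentage explicitly (recruited patients) and then uses the wrong operation.

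What is at stake is whether the plan's statements about its own robustness are true. The article uses the allowance to justify not replacing lost patients and to set aside the first limitation it lists. If losses reach the rate it assumes, the number of patients with outcomes falls below the only sample size the article derives.

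**Working it through.** **Inputs.** All come from Sample size calculation, except sidedness:

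- Difference 87 − 79 = 8 mmHg; SD 16 mmHg in both groups; standardised effect 8/16 = 0.5.
- Alpha 5%, power 80%, equal groups.
- Loss of 20% of those recruited.
- Sidedness is not stated. I assume two-sided because it is the version that reproduces the article's figure.

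**Step 1: reproduce the 64.** The two-sided independent-samples t test gives n = 63.77, rounded up to 64 per group. A one-sided test gives 50.15, rounded up to 51, which does not match. The base figure is correct.

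**Step 2: reproduce the 77.** 64 × (1 + 0.20) = 76.8, rounded to 77 per group, 154 in total. This matches the article and confirms that multiplication was used.

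**Step 3: apply the assumed loss to the 77.** 77 × (1 − 0.20) = 61.6 per group, or 123.2 of 154. That is 61 to 62 patients per group, 2 to 3 below 64.

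**Step 4: the inflation that retains 64.** 64 / (1 − 0.20) = 80 per group, 160 in total. The stated figure is 3 per group (6 in total) lower.

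**Step 5: the loss that 77 does cover.** 1 − 64/77 = 13/77 = 16.9%.

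**Step 6: effect on power** (two-sided t test, 8 mmHg, SD 16, only patients with outcomes counted):

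| Patients with outcomes per group | Power |
|---|---|
| 61 | 78.2% |
| 61.6 | 78.6% |
| 62 | 78.9% |
| 64 | 80.1% |
| 77 (no loss) | 86.9% |

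In other terms, the difference detectable with 80% power rises from 7.99 mmHg at 64 per group to 8.14 mmHg at 61.6.

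**The case against.** **The allowance was for secondary objectives, under intent to treat.** The article does say that the losses could weaken some secondary objectives and that all tests are by intent to treat. Its section on randomization describes the intent-to-treat population, in a sentence about unblinding, as all randomized subjects. A reader might therefore hold that the primary analysis keeps 77 per group and 86.9% power. Part of this stands: if final pulse pressure is obtained for most patients who stop early, the primary analysis will not fall to 61 or 62, so 78.6% is the complete-case figure at the full assumed loss. But intent to treat decides which patients belong to the analysis and does not supply a 12-week measurement for a patient who is lost. Under Statistical analysis, the article says only that missing data will be handled by a sensitivity analysis. Moreover, 64 is the only sample size it derives, so there is no other target against which 77 could be judged sufficient.

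**The plan never promised 80% power after 20% loss.** This stands. A reader might infer such a promise from the sequence of 64, 20% and 77, but no sentence makes it: 80% power is attached to 64 per group and the allowance is introduced separately. Likewise, the sentence on not replacing lost patients says that losses were predicted, which is true, and gives no number of evaluable patients. Only the Discussion claims that the loss is made good.

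**The effect is negligible.** It is about 1.5 power points, from 80.1% to 78.6%, on a loss rate that is itself a round planning assumption. The method is also disclosed. This fixes the severity at minor; it does not make the sum right.

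**Conclusion.** The point holds as a minor arithmetic error, wrong as written. With the loss defined on recruited patients, 77 per group retains 61 to 62 with outcomes at the assumed 20% loss, not 64; 80 per group would be needed. The Discussion's statement that loss to follow-up is made good does not hold against the plan's own figure.

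The 78.6% rests on four assumptions: a two-sided test, the article's 8 mmHg and SD of 16 mmHg, the full 20% loss in each group, and an unadjusted complete-case t test. With fewer losses or recovered outcomes, power lies between that value and 86.9%.

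A reader might go further and infer that the trial is underpowered, or that it fails a guaranteed 80% power after losses. The article supports neither. It gives no such guarantee, and the shortfall is 2 to 3 patients with outcomes per group. The validity of the trial is not in question.

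**What to change.** Keep 77 per group and correct the text:

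- In Sample size calculation, state that 77 per group retains 64 patients with outcomes for losses up to 16.9%, and that at 20% loss about 61 to 62 per group remain, with about 78.6% power for a complete-case two-sided t test (8 mmHg, SD 16), against 86.9% with no loss.
- In the Discussion, replace the claim that the loss is made good with one that matches: losses up to about 17% are covered, and at 20% power is slightly below 80%.
- In the section on randomization, the no-replacement sentence can stay if it refers to the corrected statement.

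The cost is two or three sentences and a slightly less favourable stated tolerance. No added enrolment is required. Recruiting 80 per group (6 more patients in total) is the alternative if the investigators want the 20% allowance to be exact; the article describes the trial as still recruiting.

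If adjustment for baseline pulse pressure is mentioned as a way to recover power, it should be given as an assumption with its range, because the article states no correlation between baseline and final values. Taking the residual SD as 16 × √(1 − r²), power at 61.6 per group is about 79% at r = 0.1, 80% at 0.2, 82% at 0.3, 89% at 0.5 and 97% at 0.7. The correction above does not depend on any of these values.

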#### Statistical analysis

The statistical analysis will comprise the following parts:

1. In descriptive analysis of the sample, quantitative variables will be expressed as measures of central tendency (mean or median) and dispersion (standard deviation or interquartile range) for symmetrical distributions; normality will be tested using Kolmogorov-Smirnov test. Appropriate transformations will be applied in cases of a non-normal distribution. Qualitative variables will be expressed as proportions with their standard error.

2. Baseline characteristics, especially those that could influence the results, will be compared using the *t* test or Mann–Whitney test for quantitative variables and the Pearson chi-squared or Fisher exact test for qualitative variables. The main variables that could influence the result of this study at initiation are age, PP, SBP, and DBP. In the case of inequality, these factors will be treated as confounding variables in the final efficacy analysis.

3. The differences between the means and their confidence interval (CI), or the median ratio and their CI, will be used as the main measure of the effect. The relative risk, absolute risk reduction, and relative risk reduction will be used as a measure of the effect for the qualitative variables. A 95% CI will be calculated for all estimations.

4. To control for possible confounding variables, linear models or linear regression will be applied for dependent quantitative variables and logistic regression models for dependent qualitative variables.

5. In all the analyses, the null hypothesis tested will be the lack of effect (difference of means = 0, RR = 1) between the experimental and the control groups. Missing data will be processed using a sensitivity analysis.

6. As this is a two-arm, placebo-controlled, parallel study, no subgroups will be analyzed to measure secondary endpoints and no interim analysis will be performed.

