#### Variables

Variables reported for trial participants include the following:

1. Demographic characteristics: sex, age, height, weight, body mass index, waist circumference, and smoking and drinking habits, at screening.

2. Antihypertensive treatment and concomitant treatments, at screening.

3. Medical history: presence of macrovascular or microvascular disease and diabetes mellitus or dyslipidemia.

4. Laboratory tests: hematology and biochemistry with kidney and liver function markers to assess that the patient meets all the inclusion criteria (screening visit).

5. BP measurement at baseline, 6 weeks, and completion (SBP, DBP, PP, and heart rate (mean of 3) while seated and 1 minute after standing). Monitoring is performed between 8 am and 10 am, before patients take their medication.

6. 24-hour ABPM (Spacelabs device, OSI systems company, US; http://www.spacelabshealthcare.com/): mean of SBP, DBP, heart rate, and PP during activity and at rest (baseline and completion). Patients take their antihypertensive medication as usual.

7. CBP, PWV, and AI at visits 1 and 3 (measured with the patient lying supine using a Sphygmocor device, AtCor Medical, Australia; http://www.atcormedical.com/).

8. Adherence to treatment (Morisky-Green test) at screening and at visits two and four.

9. Side effects: any adverse event during administration of the study drug, in particular headache and orthostatic hypotension.

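### Baseline pulse pressure enters the efficacy model only if a baseline comparison shows inequality, so the data choose the primary model and most of the available precision is forgone

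*Protocol article*

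**What the plan says.** In the protocol article, Statistical analysis, item 2 has baseline characteristics compared between arms by t or Mann–Whitney tests for quantitative variables and by chi-squared or Fisher tests for qualitative ones. It singles out four factors: "The main variables that could influence the result of this study at initiation are age, PP, SBP, and DBP". The covariate rule follows: "In the case of inequality, these factors will be treated as confounding variables in the final efficacy analysis". No p-value or size of difference defines inequality.

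Item 4 supplies the model: "To control for possible confounding variables, linear models or linear regression will be applied for dependent quantitative variables". Read with item 2, the confounders are the factors found unequal. Item 3 makes the difference in means (or a median ratio) with its confidence interval the main effect measure.

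The Sample size calculation rests on an unadjusted comparison: "In order to obtain a power of 80% to detect differences using a *t* test for independent samples". Evaluation of effectiveness says that objectives compare baseline and final values, but it gives no model and does not settle whether final PP or change in PP is analysed. No section commits to baseline PP as a covariate regardless of the baseline tests.

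**The concern.** If randomisation is sound, any baseline difference between arms is due to chance, so a test of that difference does not tell the analyst whether to adjust. What makes a covariate worth including is how well it predicts the outcome. Baseline PP can be expected to predict final PP whether or not the arms differ, and item 2 itself lists it among the variables that could influence the result.

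Two things are at stake. First, the primary model depends on the data. With no threshold and a choice of test, two analysts could follow the text and fit different models to the same trial. Second, in most trials the tests will find nothing, and the precision that baseline PP offers as a covariate goes unused. This is a rule that the article states, not a detail it leaves to an analysis plan; a plan that followed the article would inherit it.

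**Working it through.** **Inputs from the Sample size calculation.** Means: "the PP after treatment could be 87 mmHg in the placebo group and 79 mmHg in the experimental group", a difference of 8 mmHg. Spread: "both with a standard deviation of 16 mmHg". Size: "with an α risk of 5%, the sample size for each group must be 64 patients". After losses, 77 per arm.

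**Assumptions, because the article gives no figure.** Baseline-to-final PP correlation r of 0.3, 0.5 or 0.7; baseline SD 16 mmHg (the stated 16 is for PP after treatment); inequality read as p < 0.05; two-sided α.

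**Step 1: the plan's own figure.** The standard error of the difference at 64 per arm is 16 × √(2/64) = 2.83 mmHg. The exact noncentral-t power is 79.5% at 63 per arm and 80.1% at 64, so 64 reproduces.

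**Step 2: always adjusting.** Residual SD = 16 × √(1 − r²), at 64 per arm:

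| r | Residual SD (mmHg) | Power | 95% CI half-width (mmHg) |
|---|---|---|---|
| unadjusted | 16.0 | 80% | 5.6 |
| 0.3 | 15.3 | 84% | 5.3 |
| 0.5 | 13.9 | 90% | 4.8 |
| 0.7 | 11.4 | 98% | 4.0 |

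**Step 3: the rule as written.** Simulated trials, 64 per arm, with adjustment for baseline PP only if its baseline t test has p < 0.05 (rounded; repeat simulations agree within about one percentage point):

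| r | Power, rule on final PP | Power, rule on change in PP | Power, always adjust | Type I error, rule on final PP |
|---|---|---|---|---|
| 0.3 | 80% | 67% | 83% | 4.7% |
| 0.5 | 81% | 81% | 90% | 4.5% |
| 0.7 | 82% | 96% | 97–98% | 3.6% |

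The rule scarcely improves on the unadjusted test because it triggers on baseline PP in only about 5% of trials. With the 8 mmHg effect present, the unadjusted and adjusted tests disagree on significance in about 7%, 12% and 18% of trials, so the choice of model matters.

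**Step 4: all 77 per arm analysed.** The rule on final PP gives about 88%, 88% and 89%. Always adjusting gives about 90%, 94% and 99%.

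**Step 5: how large a gap can count as equal.** At 77 per arm the limit is 1.976 × 16 × √(2/77) = 5.1 mmHg. The typical chance gap is smaller: the mean absolute gap is 16 × √(2/77) × √(2/π) = 2.1 mmHg. If final PP is analysed, an unadjusted gap shifts the estimate by r times the gap. At r = 0.5 the typical shift is 0.5 × 2.1 = 1.0 mmHg, or 13% of 8 mmHg.

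**The case against.** Several fair points limit this finding.

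- **Error rate.** A reader might infer that choosing the model from the data raises the false-positive risk. It does not: the overall type I error under the rule is at or below 5%. On final PP, power also stays at about the planned 80%.
- **Change from baseline.** Evaluation of effectiveness can be read as analysing change in PP. Baseline PP is then used, and a gap is not left uncorrected but over-corrected. This stands, and at r = 0.7 the loss is small (96% against 97–98%). At r = 0.5 the change score gains nothing, since its SD is 16 × √(2 × 0.5) = 16, and at r = 0.3 it is worse than the plain t test.
- **The 5.1 mmHg gap.** A reader might take this as the usual bias. It is close to the worst case and rests on the assumed threshold and baseline SD. Entry limits on SBP and DBP could make that SD smaller. With illustrative SDs of 13 (SBP) and 9 (DBP), it is √(169 + 81) = 15.8 at zero correlation and √(250 − 117) = 11.5 at correlation 0.5, so the limit is 5.0 or 3.7 mmHg.
- **Collinearity.** PP = SBP − DBP, so the three cannot all be estimated in one model. A reader might call this a fault in the rule, but the article lists candidates and never says that all are fitted together. Any two of the three can be.
- **Secondary outcomes.** The visits for "CBP, PWV, and AI at visits 1 and 3" show that baseline values exist, but item 2 names only the main variables. An article may leave the covariates for each secondary outcome to the full plan, so their absence is no fault.

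None of this supplies an unconditional commitment to baseline PP.

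**Conclusion.** The point holds in limited form. Item 2 fixes a covariate rule that lets a test of chance differences decide the primary model, and it forgoes most of the precision that baseline PP offers. On final PP with 64 per arm, the cost is about 3, 9 and 15–16 percentage points of power at correlations of 0.3, 0.5 and 0.7. With 77 per arm analysed it is about 2, 6 and 10 points. On change in PP with 64 per arm it is about 16, 9 and 1–2 points.

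The size depends on a correlation that the article does not give. The direction does not: always adjusting was better at every value examined, on either reading of the endpoint. The objection that the estimator is not fixed in advance needs no assumed correlation. The documents do not support a claim of inflated type I error, or that baseline PP is wholly unused on every reading. The matter should be corrected, but it does not invalidate the trial.

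**What to change.** Replace the inequality sentence in Statistical analysis, item 2, with: *The primary analysis is a linear model of final clinical PP on treatment and baseline clinical PP (and age), fitted whatever the baseline comparison shows; the unadjusted difference is reported as supportive.*

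Keep the baseline comparisons as description only, with no role in selecting covariates. Do not enter PP, SBP and DBP all together, because PP = SBP − DBP exactly. Any covariates in item 4's logistic models for the binary outcomes should likewise not be selected by baseline tests; naming them can be left to the full analysis plan.

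The cost is wording, agreed before unblinding. Baseline PP is already collected, the article reports the trial as still recruiting, and the sample size stays as stated.

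### Two alternative main effect measures are allowed and none is fixed for pulse pressure, while the sample size and the null hypothesis assume a difference of means

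*Protocol article*

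**What the plan says.** All of this is in the protocol article.

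- **Effect measure.** Statistical analysis, item 3, covers quantitative variables in general. It lists a mean difference first and then the alternative: "or the median ratio and their CI, will be used as the main measure of the effect". It has no selection rule and does not mention PP separately.
- **Normality.** Item 1, on descriptive analysis: "normality will be tested using Kolmogorov-Smirnov test. Appropriate transformations will be applied in cases of a non-normal distribution".
- **Null hypothesis.** Item 5, for every analysis: "the null hypothesis tested will be the lack of effect (difference of means = 0, RR = 1". The first null is for quantitative outcomes and the second for proportions. There is none for a ratio of medians.
- **Named tests.** Item 2 has a parametric and a rank-based option, but only for baseline characteristics, which "will be compared using the *t* test or Mann–Whitney test for quantitative variables". Item 2 also makes adjustment for age and baseline pressures depend on whether the arms are found to differ. Item 4 uses linear models for quantitative outcomes.
- **Planning.** Sample size calculation: "the PP after treatment could be 87 mmHg in the placebo group and 79 mmHg in the experimental group", SD 16 mmHg in both arms, independent-samples t test, 64 per group, raised to 77 for losses.
- **Success criterion.** Evaluation of effectiveness asks for a significant fall in PP against placebo and names no scale or measure.

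**The concern.** A difference of means and a ratio of medians are different quantities on different scales. The planning values give 79 − 87 = −8 mmHg on one and 79/87 = 0.908 on the other. If the transformations in item 1 reached PP, there would be a third scale.

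Leaving the choice open has three consequences. The trial has not said what its primary result estimates. The stated 80% power holds for one of the two measures only. And if the choice is made once outcome data are at hand with no rule written down, the measure can be picked with knowledge of the result. The normality testing and transformations in item 1 leave room for a data-driven choice, although they are not stated to be the selector.

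**Working it through.** **Inputs.** Means 87 and 79 mmHg, SD 16, alpha 5%, power 80%, 64 and 77 per group, losses 20%: all from the Sample size calculation. Not in the document and assumed here: the test of the median ratio (log ratio with a bootstrap standard error), the switching rule, and the skewed distribution.

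**1. The plan's own figure.** n = 2(1.960 + 0.842)² × 16²/8² = 2 × 7.85 × 4 = 62.8, so 63 by the normal approximation. The exact t calculation gives 63.77, so 64 as stated. A one-sided test would give 50, so the plan is two-sided. 64 × 1.20 = 76.8, so 77. Power of the t test for 8 mmHg is 80.1% at 64 per arm and 86.9% at 77. The planned size therefore fits a difference of means.

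**2. The same size with medians, normal data.** The standard error of a median is √(π/2) = 1.253 times that of a mean, so z = (8/16) × √(n/2) / 1.253.

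- n = 64: z = 2.828/1.253 = 2.257, power = Φ(2.257 − 1.960) = 61.7%.
- n = 77: z = 3.102/1.253 = 2.475, power = Φ(2.475 − 1.960) = 69.7%.
- Simulating the log median ratio itself (2,000 trials) gives 59.8% and 66.1%.
- Size needed for 80%: 64 × π/2 = 100.5, so about 101 per arm.

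**3. What a choice between the two measures does.** Simulation, 2,000 trials per scenario, 64 and 77 per arm, normal data and a shifted lognormal with log-SD 0.5. The rule-based switch leaves the t test when a Kolmogorov-Smirnov type (Lilliefors) test rejects normality in either arm. The simulation error on a 5% rate is √(0.05 × 0.95/2000) = 0.5 percentage points.

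| Way of choosing | Type I error |
|---|---|
| Rule-based switch, t test to median ratio | 5.3–5.9% |
| Rule-based switch, t test to Mann–Whitney | 4.7–5.7% |
| Whichever of t test and median ratio is significant | 8.1–8.9% |

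Power for 8 mmHg under the rule-based switch to the median ratio:

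- Normal data: the switch triggers in about 5–7% of trials, and power is 78% at 64 and 84% at 77.
- Skewed data: the switch triggers in about 94–98% of trials, and power is 76% and 81%, against 81% and 86% for the t test throughout.

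**4. Whether the mean comparison needs a normality condition.** With gamma data of skewness 1, the t test's simulated type I error was 5.3% and 4.9% at 64 per arm in two separate runs, and 4.4% at 77. It does not need one at this size.

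**The case against.** The strongest reply is that, read as a whole, the article points to means for PP. The t test is the only test tied to PP, the null is on means, and the adjustment models are linear. Item 3 is general and its alternative may be meant for other variables, such as augmentation index or pulse wave velocity. The analyst is blind to group (Randomization, blinding, and assignment to treatment groups), which limits scope for favouring a result. The article is condensed, and a statistical analysis plan that is not shown may settle the matter.

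Most of this stands as mitigation. It does not remove the defect: item 3 states an either/or for the main measure, PP falls under it by default, and items 3 and 5 do not match each other. Blinding limits selective choice but does not say which quantity is estimated.

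A reader might go further and infer that the Kolmogorov-Smirnov test decides between the mean difference and the median ratio, so that the primary measure flips almost at random. The text does not support that. Item 1 puts the test under description and answers non-normality with transformation, not with medians. Nor would such a gate produce the 62% power figure. The ordinary test with estimated mean and SD, run on 128 values, rejected 0.0% of normal samples and 14% at skewness 1, so it would almost always keep the mean. A Lilliefors-corrected version rejected 81% at skewness 1. The article does not say which version is meant. Skewness 1 is itself an assumption: a gamma distribution with mean 87 and SD 16 has skewness 2 × 16/87 = 0.37.

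**Conclusion.** The concern holds as an unresolved choice and an internal mismatch. Item 3 permits two main measures without saying which applies to PP, and one of them agrees with neither the sample size calculation nor the null in item 5.

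The size is moderate. If the median ratio became the main measure with normal data, power would be about 60–62% at 64 per arm and 66–70% at 77, against 80% and 87%. A fixed switching rule would do little harm to type I error. Only free choice of the significant measure brings it to about 8–9%, and the article does not say that this is intended. It is also too strong to infer that the primary test is left open, since Mann–Whitney appears only for baseline comparisons.

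The planning power rests on the article's figures. The median-ratio and switching results rest on the assumed bootstrap test, switching rule and distributions given above.

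**What to change.** Reword items 1 to 3 and 5 so that:

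- The single primary effect measure is the baseline-adjusted difference in mean week-12 clinic PP, in mmHg with 95% CI, whatever the distribution of the data and whatever the baseline comparisons show. The null in item 5 then fits as it stands.
- Normality testing and transformation are stated not to govern the primary PP analysis.
- A median or rank-based analysis of PP is kept as a named sensitivity analysis.
- If the median ratio is wanted for other quantitative outcomes, item 3 names them and item 5 gives its null (ratio = 1).

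The cost is wording only. Trial status reports that recruitment is under way, so the change can be made before unblinding. The sizes of 64 and 77 need no change on this account, since they were calculated for a difference of means. The article gives no correlation between baseline and final PP, so no gain in power from the adjustment is claimed.
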